The identification, screening and enrolment logs, linking participant identifiable data to the pseudoanonymised Participant Identification Number, will be held locally by the research sites. Trial data will be recorded, using the Participant Identification Number, on an electronic Case Report Form (eCRF) developed using MS Visual Basic.NET/ASP.NET 2012 and MS SQL Server.

Remote monitoring will be performed during the trial to ensure quality and consistency of data. A data management plan has been developed; this contains further information on data collection and cleaning, and will be reviewed and updated during the trial.

### Patient characteristics

Patients of either gender, aged 40 years or older, are being entered into the trial. Patients are considered to have IPF following a multidisciplinary team (MDT) consensus decision undertaken at a specialist centre (or MDT otherwise meeting the criteria of a specialist centre) following a review of an appropriate clinical history, characteristic features of usual interstitial pneumonia (UIP) on thoracic, high-resolution computed tomography (HRCT) and/or UIP histology confirmed by surgical lung biopsy according to the latest international guidelines [6]. There is no maximum time limit between the diagnosis of IPF and enrolment. Patients may receive orally administered prednisolone at a dose of up to 10 mg per day (in keeping with previous studies [11]), anti-oxidant therapy, pirfenidone, nintedanib or other licensed medication for IPF. If taking licensed medication for IPF, patients should be on a stable treatment regimen for at least 4 weeks prior to the screening visit to ensure that baseline values are representative. Patients must also have a Medical Research Council (MRC) Dyspnoea Score [16] of greater than 1, with this being defined as ‘Not troubled by breathlessness except on strenuous exercise’, at screening in order to exclude asymptomatic patients.

Patients with a FVC of more than 75%, as predicted based on the algorithm suggested by Crapo et al. [17] are not recruited into the trial; this is intended to exclude patients with mild disease and, instead, to identify patients more likely to meet the primary endpoint (see ‘Sample size’ section). Other reasons for exclusion include (1) a recognised significant co-existing respiratory disease, e.g. obstructive airways disease (defined as forced expiratory volume in 1 s (FEV_1_)/FVC < 60% [18]), (2) a significant medical, surgical or psychiatric condition that would affect subject safety or influence the trial outcome or (3) untreated folate or vitamin B_12_ deficiency, to ensure that no bone marrow or neurological adverse effects occur with folate therapy to vitamin B_12_-deficient individuals. Sulphonamides are recognised to increase the risk of haemolysis in individuals with glucose-6-phosphate dehydrogenase (G6PD) deficiency although this risk remains low [17]. The prevalence of G6PD deficiency is higher in men of African, Asian or Mediterranean descent and, therefore, patients in these demographics are screened for the condition and, if found to have G6PD deficiency, are excluded from the trial. Patients with a self-reported respiratory tract infection within 4 weeks of screening (defined as two or more of cough, sputum or breathlessness and requiring antimicrobial therapy) are not eligible due to the difficulty of obtaining reliable baseline lung function. Those patients receiving a short course of antibiotics (for any indication) within 4 weeks of screening or long-term prophylactic antibiotic treatment (defined as more than 1 month of therapy) within 3 months of screening are also ineligible as this may have an impact on lung microbiota. A risk of sudden death in patients treated with co-trimoxazole and angiotensin-converting enzyme (ACE) inhibitors was identified [19] and is thought to be due to an increase in serum potassium due to an amiloride-like action of trimethoprim on sodium channels in the distal nephron [20]. For this reason, patients with a serum potassium greater than 5.0 mmol/L are excluded and patients with a baseline serum potassium of between 4.7 and 5.0 mmol/L, who are 66 years old or over and taking potassium-sparing diuretics (including ACE inhibitors or angiotensin-receptor blockers), are required to have an extra blood test to measure potassium 1 week after starting trial treatment.

### Identification, recruitment and randomisation

The main method of patient identification is by review of ILD MDT meeting minutes or summaries, but is also via screening patient registries, hospital medical records and databases of research-interested patients. Potential recruits are being approached by local clinic teams and provided with a patient information sheet and given at least 24 h to read this prior to consent. Consent is taken by appropriately-trained clinicians or delegated members of staff. All patients are invited to provide additional consent to provide a sample of blood for deoxyribonucleic acid (DNA) analysis; however, this is optional and patients can refuse whilst remaining eligible for the main trial.

Following consent, patients meeting all inclusion criteria and none of the exclusion criteria (after review of their screening bloods) may be randomised without a subsequent visit. Randomisation is performed centrally according to a computer-generated randomisation code with the treatment group allocation sent to research pharmacists only. Minimisation factors are: research site and the use of baseline licensed medication for IPF.

### Interventions

Participants receive co-trimoxazole (generic) 960 mg as two tablets of 480 mg twice a day plus folic acid 5 mg once a day or placebo tablets (manufactured to appear identical to co-trimoxazole 480 mg) two oral tablets twice a day plus folic acid 5 mg once a day over a median treatment period of 27 (range 12–42) months. This is dispensed 3-monthly for the first 6 months then 6-monthly and supplied in bottles providing 1 month’s supply either by hospital pharmacy or via a courier. Participants are advised to store their medication below 25 °C but there will be no temperature monitoring after dispatch to the patient. Folic acid must be taken by participants whilst on the trial drug to reduce the risk of bone marrow depression associated with the long-term use of co-trimoxazole.

The trial drug may be reduced to two tablets once a day three times a week plus 5 mg folic acid once a day three times a week if patients develop gastrointestinal adverse effects or rash, have grade 1 hyperkalaemia (serum potassium > 5.0 mmol/L and < 5.5 mmol/L) or any other adverse event that, in the opinion of the local investigator, requires a dose reduction. In such cases, the dosing interval is to ensure that the dosing is spread throughout the week (e.g. Monday, Wednesday and Friday or equivalent). Once a patient has had their dose reduced, no re-escalation will be permitted, even if the adverse event leading to the reduction resolves.

Compliance to trial treatment in the form of returned tablet counts is being monitored as part of drug accountability at each visit. Patients are permitted to receive *N*-acetyl cysteine and anti-oxidants, short-term prednisolone (any dose), long-term prednisolone (up to a dose of 10 mg per day) and licensed treatments for IPF. All concomitant medication is being recorded at baseline and change in concomitant medication recorded at each visit. Patients are permitted to receive other medications (e.g. for other conditions), but non-permitted therapies include: amiodarone, azathioprine, mycophenolate mofetil, cyclophosphamide, methotrexate, D-penicillamine, colchicine, clozapine, methenamine, dapsone, gamma-interferon, cyclosporin, mercaptopurine, repaglinide, pyrimethamine, lamivudine, typhoid vaccination or unlicensed medication. Therapies requiring caution or increased monitoring include: digoxin, warfarin, phenytoin, sulphonylureas and procainamide hydrochloride. Increased monitoring of potassium is required for patients commenced on medication that increases serum potassium concentration.

### Primary outcomes

The primary outcome is the time to death (all causes), transplant or first non-elective hospital admission. Individuals who withdraw will be censored on the date of withdrawal.

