**Methods/design:**

The EME-TIPAC trial is a double-blind, placebo-controlled, randomised, multicentre clinical trial.

A total of 330 symptomatic patients, aged 40 years old or older, with IPF diagnosed by a multidisciplinary team (MDT) according to international guidelines and a FVC ≤ 75% predicted will be enrolled. Patients are randomised equally to receive either two tablets of co-trimoxazole 480 mg or two placebo tablets twice daily over a median treatment period of 27 (range 12–42) months. All patients receive folic acid 5 mg daily whilst on the trial IMP to reduce the risk of bone marrow depression.

The primary outcome for the trial is a composite endpoint consisting of the time to death, transplant or first non-elective hospital admission and will be determined from adverse event reporting, hospital databases and the Office of National Statistics with active tracing of patients missing appointments. Secondary outcomes include the individual components of the primary outcome, (1) King’s Brief Interstitial Lung Disease Questionnaire, (2) MRC Dyspnoea Score, (3) EQ5D, (4) spirometry, (5) total lung-diffusing capacity and (6) routine sputum microbiology. Blood will be taken for cell count, biochemistry and analysis of biomarkers including C-reactive protein and markers of disease.

The trial will last for 4 years. Recruitment will take place in a network of approximately 40 sites throughout the UK (see Table 1 for a full list of participating sites). We expect recruitment for 30 months, follow-up for 12 months and trial analysis and reporting to take 4 months.

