## Methods/design

The trial is a phase III, double-blind, parallel-group, 1 to 1 randomised, placebo-controlled, multicentre clinical superiority trial of orally administered co-trimoxazole versus placebo in patients with moderate to severe (FVC ≤ 75% predicted) IPF, with outcomes assessed over a median treatment period of 27 (range 12–42) months. Participants receive co-trimoxazole or placebo until they meet a primary endpoint event, they withdraw consent, or the trial concludes. This trial is designed to align with routine care as much as possible and the trial visits are intended to coincide with routine clinical follow-up visits. Follow-up of assessment measures will continue for the duration of the trial for those participants stopping trial medication due to adverse events or patient choice. The vital status and details of admission to hospital will be captured for all patients who have consented to participate in the trial regardless whether they have withdrawn from the intervention or trial assessments.

Figure 1 provides a study flowchart of the trial design and Fig. 2 provides the time and event schedule. The trial protocol (v3.0, dated 16 May 2016) is based on the Standard Protocol Items: Recommendations for Interventional Trials (SPIRIT) 2013 Statement for protocols of clinical trials (see Additional file 1).

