### Statistical analysis

All analyses will be conducted according to a detailed statistical analysis plan. Analyses will be adjusted for site and the use of baseline, licensed medication for IPF. The analysis populations are defined as intention-to-treat (all randomised individuals regardless of adherence), per-protocol (all randomised individuals who adhere to the trial medication to within 80% (based on pill counts)), modified-per-protocol (all randomised individuals who adhere to the high-dose regimen) and safety population (all patients randomised who received at least one dose of the trial treatment). Non-compliance will be dealt with using a Compliance-Adjusted-Causal-Effect (CACE) analysis, using compliance data from returned medication (pill counts).

The primary outcome will be analysed using a Cox proportional hazards model adjusted for the variables included in the minimisation algorithm (baseline licensed IPF medication and site). The results will be presented as the Kaplan-Meier estimate of the survival function for each treatment arm separately and, if appropriate, the median will be estimated. The treatment effect size will be the hazard ratio and estimated with 95% confidence intervals and *p* values.

At each relevant time point from 6 weeks post randomisation, the K-BILD, EQ5D, LCQ, spirometry (FVC per cent predicted, FEV per cent predicted, FVC absolute value, FEV absolute value and FVC/FEV ratio) and DLCO will be analysed using linear model to compare the average values between the treatment arms adjusted for the variables included in the minimisation algorithm: baseline disease-modifying therapy and site will be included as a random effect. The effect size will be the mean difference and will be presented with 95% confidence intervals and *p* values.

The MRC Breathlessness Score and cough score will be analysed using a Mann-Whitney test to compare the distribution of the score between the treatment arms. A generalised effect size will be estimated and presented with 95% confidence intervals and *p* values.

The safety analysis will be based on the pre-defined population (as above). Summary tables will be presented for incidence rates (number of patients with at least one incidence) of adverse events and serious adverse events coded according to the Medical Dictionary for Regulatory Activities (MedDRA). Tables of change from baseline will be presented for the blood and other clinical laboratory assessments.

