## Discussion

IPF is a progressive and usually fatal lung disease with a 5-year survival of 20–40% [36]. The aetiology for the majority of patients is unclear and there are limited treatment options. The EME-TIPAC trial should determine whether the addition of co-trimoxazole to current standard care improves patient-relevant outcomes in moderate and severe disease and should explore how co-trimoxazole may be working.

There is much debate about the choice of primary endpoint for clinical trials of IPF. Our primary outcome of time to death (all causes), transplant or first non-elective hospital admission is clinically important. These endpoints have been recommended by the Pulmonary Fibrosis Foundation for phase 3 clinical trials in IPF [37]. Many trials use surrogate markers of disease progression, most commonly lung function measures such as FVC. These have the advantage that they are inexpensive and relatively easy to determine, but are not reliable, validated or adequately robust [37]. Some researchers have claimed that the change in FVC should be used as an endpoint, claiming that a mortality endpoint requires unfeasibly large studies in mild to moderate IPF [38]. The situation is, however, different when evaluating patients with severe disease. In a meta-analysis of placebo data of clinical trials of IPF, annual mortality in studies selecting mild-moderate patients was 8%, but in trials including moderate-severe patients it was 19% [39], in keeping with the data from TIPAC [14] and the epidemiology of the disease [2]. The event rate of mortality and hospitalisations is even higher when selecting patients with severe disease (up to 16% in 3 months [40]). Our primary outcome also meets the European Medicine Agency criteria for composite endpoints, as hospitalisation is an important predictor of mortality [25]. It can be easily and reliably assessed without patient involvement and is the least likely criterion to be influenced by withdrawal from the trial or unintentional or unavoidable unblinding of patients.

We have chosen to evaluate health-related quality of life by a number of different tools. All of the questionnaires are short and easy to complete, as we are cognisant of research participant burden. We decided against using the St. George’s Respiratory Questionnaire: although this has been used in a number of clinical trials [41], it takes nearly 10 min, and participants find difficulty completing it unaided [7].

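### The primary outcome is censored at withdrawal although deaths and admissions after withdrawal are still collected, which discards known events and invites informative censoring

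*Protocol article*

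**What the plan says.** The Primary outcomes section defines the outcome as time to death, transplant or first non-elective admission and gives one censoring rule: "Individuals who withdraw will be censored on the date of withdrawal". It sets no limit on the type of withdrawal.

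Other parts of the protocol article point the other way:

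- **Methods/design, data capture.** "The vital status and details of admission to hospital will be captured for all patients who have consented to participate in the trial", and this holds "regardless whether they have withdrawn from the intervention or trial assessments".
- **Methods/design, stopping the drug.** "Follow-up of assessment measures will continue for the duration of the trial for those participants stopping trial medication due to adverse events or patient choice".
- **Abstract, Methods/design.** Primary events come from adverse event reports and from "hospital databases and the Office of National Statistics with active tracing of patients missing appointments".
- **Discussion.** The endpoint is preferred partly because it can be assessed without the patient's involvement and "is the least likely criterion to be influenced by withdrawal from the trial".
- **Statistical analysis.** One analysis population is "intention-to-treat (all randomised individuals regardless of adherence"). The primary model is a Cox model adjusted for site and baseline licensed IPF medication. Nothing in this section restores events that occur after withdrawal.

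**The concern.** The trial pays for record-based follow-up that does not depend on the patient attending, and then ends the patient's follow-up time at withdrawal. Two consequences follow.

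1. **Events are lost.** A death or emergency admission after withdrawal is recorded but does not count.
2. **Censoring may be informative.** A Cox model treats a censored patient as having the same future hazard as patients in the same arm, with the same covariates, who remain at risk. In moderate to severe IPF, patients who leave may well be those who are deteriorating. If the link between withdrawal and prognosis differs by arm, the hazard ratio is biased. If frailer patients leave the active arm more often, co-trimoxazole looks better than it is.

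The estimate would also stop matching an intention-to-treat comparison. Every randomised patient stays in the denominator, but follow-up after withdrawal is removed by rule even where it exists.

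**Working it through.** **1. The plan's own figure.** The Sample size section gives medians of 28.8 and 51.1 months, two-sided 5%, 80% power and 96 events. With HR = 28.8/51.1 = 0.5636, Schoenfeld's formula gives D = 4 × (1.96 + 0.8416)² / (ln 0.5636)² = 95.5, so 96 events. The figure reproduces and is not at fault.

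**2. Events lost.** Inputs from the protocol article: the medians above, 1:1 allocation, uniform entry over 30 months plus 12 months' further follow-up (so 12 to 42 months per patient), and N = 330 to be randomised or N = 264 as in the Sample size section. Assumptions: exponential event times, and a constant withdrawal hazard η unrelated to prognosis. The documents give no withdrawal rate.

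For each arm, with λ = ln 2 / median (0.02407 control, 0.01356 active) and θ = λ + η:

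P(event counted) = (λ/θ) × [1 − (e^(−12θ) − e^(−42θ)) / (30θ)]

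Expected events D = (N/2) × sum over the two arms. Power = Φ(|ln 0.5636| × √D / 2 − 1.96).

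- No withdrawal censoring: arm probabilities are 0.4664 and 0.3019, so D = 165 × 0.7683 = 126.8 at N = 330.
- 20% withdrawing by 27 months: η = −ln(0.8)/27 = 0.00826. The probabilities become 0.4211 and 0.2705, so D = 165 × 0.6916 = 114.1.

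| Assumed withdrawal | D, N = 330 | Power | D, N = 264 | Power |
|---|---|---|---|---|
| none, or all events counted | 126.8 | 0.898 | 101.4 | 0.823 |
| 5% by 27 months | 123.7 | 0.890 | 98.9 | 0.814 |
| 10% by 27 months | 120.5 | 0.883 | 96.4 | 0.804 |
| 20% by 27 months | 114.1 | 0.865 | 91.3 | 0.782 |
| 30% by 27 months | 107.5 | 0.844 | 86.0 | 0.757 |
| 20% by 12 months | 100.9 | 0.821 | 80.7 | 0.731 |

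The last row is severe: the same hazard implies 1 − 0.8^(27/12) = 39.5% withdrawn by 27 months.

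**3. Bias.** This is a Cox simulation with 400,000 patients per case and a true HR of 1.00. Both arms have the control-arm hazard multiplied by a log-normal frailty (SD 0.8 on the log scale), and follow-up is uniform on 12 to 42 months. Withdrawal on placebo is unrelated to frailty. On the active arm the withdrawal hazard is multiplied by frailty or by frailty squared. About 160,000 events give a standard error for ln HR of about 2/√160,000 = 0.005, so simulation error is about ±0.01.

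| Nominal withdrawal by 27 months, placebo / active | Link to frailty (active arm) | Estimated HR |
|---|---|---|
| all events counted | – | 0.99 |
| 20% / 20% | none | 1.00 |
| 20% / 20% | frailty | 0.96 |
| 10% / 30% | frailty | 0.94 |
| 20% / 20% | frailty squared | 0.91 |
| 10% / 30% | frailty squared | 0.86 |

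With a patient-level HR of 0.56, counting all events gives a population HR of 0.60. The four frailty-linked cases give 0.57, 0.55, 0.53 and 0.50 in the same order.

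The direction is not fixed. With a frailty SD of 0.7 and about 18% to 22% withdrawn on active against 10% on placebo, a true null gave 1.02 to 1.04 when fitter active-arm patients left; a separate run of that pattern gave 1.06. It gave 0.96 when frailty drove withdrawal in both arms.

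**The case against.** The strongest reply is that the word for withdrawal is undefined. Methods/design distinguishes stopping the drug, withdrawing from the intervention or assessments, and withdrawing consent. If the censoring sentence means only full withdrawal of consent to data use, censoring cannot be avoided and the conflict largely disappears. That reading is possible, but the sentence does not state it. The only statement about follow-up after withdrawal covers the intervention and the assessments. Left undefined, the word allows two different primary analyses, so the sentence needs correcting under either reading.

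Other points on that side stand in part:

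- **Tolerability as a cause of unequal withdrawal.** The trial is double-blind. The Interventions section allows dose reduction for gastrointestinal effects, rash and grade 1 hyperkalaemia, and patients who stop the drug remain in follow-up. Such patients need not become withdrawals, so this mechanism is plausible but not shown.
- **Power.** At N = 330 every case above stays over 96 events and 80% power. Power falls below 80% only at N = 264 with about 20% withdrawal or more. The ratio 264/330 = 0.80 would fit a 20% loss allowance, but the article does not say so.
- **Direction of bias.** It depends on who leaves and from which arm, and the documents give no such information.
- **Intention to treat.** The Statistical analysis section defines this population without naming it as the primary set, and censoring removes no patient from it. What is lost is follow-up time and events.
- **The analysis plan.** It may define types of withdrawal. That does not excuse a rule stated here without limit and in conflict with the article's own data capture.

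**Conclusion.** The concern holds and should be corrected before analysis. It rests on the text: an unqualified rule to censor at withdrawal, set against continued capture of deaths and admissions after withdrawal and a defence of the endpoint on exactly that ground. The loss of power is modest at N = 330: about 1 to 5 percentage points for 5% to 30% withdrawal by 27 months, and about 8 points in the severe case. The more serious cost is an avoidable assumption that withdrawal is unrelated to prognosis. Under the frailty-linked active-arm patterns shown, a null effect appears as HR 0.96 to 0.86. Other patterns give no bias or a bias against co-trimoxazole. These figures illustrate what is possible and do not predict the trial's result. Counting the captured events removes the problem except where consent to use of records is itself withdrawn.

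**What to change.** Replace the censoring sentence in the Primary outcomes section with wording such as:

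> Participants who stop treatment or trial assessments stay in follow-up for death, transplant and non-elective admission through records and tracing. They are censored only at the end of the trial or at the date on which consent to use of their records is withdrawn.

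Define the types of withdrawal once (from treatment, from assessments, from use of records) and use the same terms in the analysis plan. Name transplant among the traced events, because the capture statement lists only vital status and admissions. Keep censoring at withdrawal as a labelled sensitivity analysis, and report the number of each type of withdrawal by arm.

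The cost is one sentence in the protocol and a matching one in the analysis plan. Methods/design already provides for collecting deaths and admissions. The article says analysis details are finalised before database lock, so the change can be made then, before allocation is known.
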